### The primary outcomes for the study are to

1. Increase the proportion of women (15%) reporting that they have been asked about family violence or nurses reporting they have screened for family violence (i.e. questions from the Key Ages and Stages protocol)

2. Increase the proportion of women disclosing IPV (discussing IPV with MCH nurse) or nurses reporting discussing safety plans

3. Increase the proportion of referrals reported by nurses or women reporting being offered referrals

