### Secondary outcomes are to

1. Estimate the prevalence of any IPV in the previous 12 months (measured with the Composite Abuse Scale, ≥3-6, and ≥7), IPV during pregnancy and any reported child abuse

2. Increase the proportion of MCH clients reporting satisfaction with quality of care and support they receive for themselves, their partners and their children

3. Investigate the proportions of women reporting any harm arising from (a) responding to questions about IPV in their MCHN consultation or (b) responding to questions about IPV in the survey)

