#### Survey sample size calculation

(b) We calculated that around 8-10% of women attending each of the eight MCH services will have been abused in the previous 12 months [4]. Following twelve months implementation, we will send a mailed questionnaire to all women who have given birth in the previous 8 months in both the comparison and intervention municipalities (5000 per arm). This sample size enables us to detect a predicted increase of 15% average disclosure found previously in a screening intervention of screening vs usual care [27]. We have taken into account both the numbers of births in participating local government areas (using most recent published data (2005), the likely response fraction (55-65% following mailed surveys and a reminder postcard - a modified Dillman procedure) and also adjusted for clustering. We adjusted for an intra-cluster correlation of 0.02 from a previous IPV primary care study [28].

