#### Survey measures

The survey booklet ‘Women’s Experiences of Health Care and Support with a New Baby’ has seven sections: (A) About your baby; (B) About your own health following your baby; (C) Your health care support; (D) Other care and support you receive; (E) Relationships and family; (F) You and your partner; (G) About you. It is designed to maximize women’s safety as it is mailed to her home. Section F includes questions about intimate partner violence measured using Hegarty’s Composite Abuse Scale [29], together with questions about being asked, disclosure (and comfort to disclose), rates of referral and satisfaction measures for herself, her children and in relation to strategies for her partner.

The questionnaire also includes depression and anxiety measures using the DASS-21 [30,31]; women’s experiences of motherhood measured with the Experience of Motherhood Scale [32] and a range of other assessments of women’s experiences.

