### Maternal health checklist

Evidence from the systematic review suggested that women preferred self-completion screening methods (e.g. paper or computer based) rather than face-to-face screening inquiry (ref). The maternal health checklist was developed as a tear-off pad consisting of an A-5 set of questions for women to self-complete at the agreed consultation which focused on maternal health, rather than the development of the baby, who is the MCH nurses’ primary client. When women arrived at this visit, they were given the checklist and asked to complete it in a quiet corner and let the nurse know when finished. The checklist consists of a set of questions about maternal health, beginning with questions about physical health, such as headache, nipple or bowel problems then moving to those about depression, contraception or drug misuse to the same family violence questions being asked as part of the Key Ages and Stages (KAS) mandatory screening at four weeks. After discussion, MOVE added two further questions to this list. Just before the KAS questions, we added:

*Do you have any problems in your relationships or intimacy with your partner?* and *Has anyone in your household ever humiliated you or tried to control what you can or cannot do?* The first question was seen as useful for women who may want to discuss non-specific problems in the relationship prior to disclosure and the latter because it is central to intimate partner abusive behavior. If a woman ticked any of the relationship or any family violence questions, nurses were asked to initiate a discussion about these in ways that felt appropriate and comfortable. The completed checklist form is retained as part of the study data collection.

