### Data analysis and reporting

#### Women’s survey

The MCH consumer survey data will be cleaned, double-coded and entered into a secure database by an external company blinded to the study arms. It will then be forwarded to a statistician blinded to study arm. Women’s characteristics for socio-demographic and birth characteristics will be compared by trial arm to ensure that randomization was effective. The representativeness of the women responding to the survey (i.e. sample bias due to differential study participation rates) will be assessed by comparison with routine perinatal data for all women giving birth in the region for the comparison year (Victorian Perinatal Data Collection Unit, DHS).

All data will be analyzed by intention-to-treat and variance estimates in models will be adjusted for the effect of the clustered (LGA) selection of participants. We will analyze data using contingency table analyses for bivariate and binary logistic regression with robust standard errors for multivariate models. For primary outcomes, we will analyze data stratified by and adjusted for women’s abuse status and for potentially significant confounding variables (where randomization is less effective in removing bias across study groups), including women’s socio-economic status.

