##### For MOVE primary outcomes

we will report:

• Any difference in proportions by trial arm (from survey and routine data) of screening for IPV (questions about fear of a partner; physical abuse and concern about the safety of their children) will be reported separately and as a screening inquiry composite variable

• Any difference in proportions by trial arm of women reporting IPV (Composite Abuse Scale ≥ 3 and ≥7) who have discussed IPV with their MCH nurse

• Any difference in proportions by trial arm of nurses who have reported that they have made safety plans with women clients

• Any difference in proportions by trial arm of women reporting IPV (Composite Abuse Scale ≥ 3 and ≥7) who have been offered a referral (if sufficient numbers) or nurses who report they have made referrals for IPV (routine data)

The following measures will be reported for the overall population and also by trial arm.

• Any difference in proportions by trial arm of abused and non-abused women reporting satisfaction with their MCH nursing care

• Intimate partner violence measured by the Composite Abuse Scale reported for women with scores ≥ 3 and those with scores ≥ 7

• Proportions ever having been afraid and currently afraid of their partner

• Proportions reporting partner abuse during pregnancy for the recent pregnancy and any in a past pregnancy.

• Proportions abused in pregnancy by family members and by other known persons (e.g. employer, housemate)

• Proportions physically, sexually, emotionally abused or neglected as children

• Proportions reporting harm from IPV screening or participating in an IPV screening study

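### Survey primary outcomes are conditioned on abuse status measured after allocation, in the same questionnaire, so the arm comparison can be distorted in a direction the protocol cannot tell us

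*Protocol article*

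**What the plan says.** Data analysis and reporting, Women's survey: "For primary outcomes, we will analyze data stratified by and adjusted for women’s abuse status". The same sentence adds potential confounders such as socio-economic status. The section also promises an intention-to-treat analysis and bivariate contingency tables.

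For MOVE primary outcomes: survey disclosure is reported for "women reporting IPV (Composite Abuse Scale ≥ 3 and ≥7) who have discussed IPV with their MCH nurse". Survey referral is reported for "women reporting IPV (Composite Abuse Scale ≥ 3 and ≥7) who have been offered a referral (if sufficient numbers"). Screening inquiry is reported by arm without a CAS restriction. Safety plans and nurse-reported referrals carry no CAS restriction either. CAS ≥3 and ≥7 prevalence is to be reported overall and by arm.

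The primary outcomes list defines the second outcome without the restriction: "Increase the proportion of women disclosing IPV (discussing IPV with MCH nurse) or nurses reporting discussing safety plans".

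On timing, Survey sample size calculation says: "Following twelve months implementation, we will send a mailed questionnaire to all women who have given birth in the previous 8 months". Survey measures places the CAS in Section F of that booklet, beside the items on being asked, disclosure and referral. The CAS window is given under Secondary outcomes: "Estimate the prevalence of any IPV in the previous 12 months (measured with the Composite Abuse Scale, ≥3-6, and ≥7"). No measure of abuse in these women before the intervention is described.

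**The concern.** A covariate, stratifier or denominator keeps the randomised comparison intact only if allocation cannot change it. Survey abuse status does not meet that condition. Its most plausible route of change is recognition and reporting. Only intervention women complete the MOVE checklist, which adds the item "Has anyone in your household ever humiliated you or tried to control what you can or cannot do" to the mandated questions, and ticking it is meant to start a discussion. A woman led to name such behaviour may later answer an abuse scale differently. A change in abuse itself after support or referral is a second, weaker route.

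If the share or type of women scoring CAS-positive differs by arm for these reasons, the CAS-restricted disclosure and referral rates compare unlike groups. The inquiry outcome, adjusted for the same variable, has a milder form of the problem. The all-women outcome named in the primary outcomes list and the CAS-restricted one in the reporting list are also different quantities, and the article does not say which one leads.

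**Working it through.** **1. When abuse status is measured.** The survey follows twelve months of implementation and contains both the CAS and the outcomes. Stratifier, covariate and denominator are all post-allocation.

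**2. Individual exposure.** Respondents gave birth in the previous 8 months, and the MOVE visit is at three or four months. The longest time since that visit is about 8 − 3 = 5 months, so at least 12 − 5 = 7 months of the CAS window precede it. This weakens the route through changed abuse. It does not weaken the route through changed reporting.

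**3. Can a difference be created?** Let d be true disclosure among abused women, a the chance that a discloser scores CAS-positive, and s the same chance for a non-discloser.

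Restricted rate = d·a / [d·a + (1 − d)·s]

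Assume d = 20% in both arms, so the true difference is zero. All values of a and s are assumptions.

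| Comparison arm | MOVE arm | Restricted rates, MOVE v comparison | False difference |
|---|---|---|---|
| a = s = 0.7 | a = 0.8, s = 0.7 | 0.16/0.72 = 22.2% v 20% | +2.2 |
| a = s = 0.7 | a = 0.9, s = 0.7 | 0.18/0.74 = 24.3% v 20% | +4.3 |
| a = 0.9, s = 0.7 | a = 0.9, s = 0.7 | 24.3% v 24.3% | 0 |
| a = s = 0.7 | a = s = 0.9 | 0.18/0.90 = 20% v 20% | 0 |
| a = 1, s = 0.8 | a = 1, s = 0.9 | 0.20/0.92 = 21.7% v 23.8% | −2.1 |
| a = 1, s = 0.8 | a = 1, s = 1.0 | 20% v 23.8% | −3.8 |
| a = 1, s = 0.8 | a = 1, s = 0.6 | 0.20/0.68 = 29.4% v 23.8% | +5.6 |

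The sign depends on who changes their reporting.

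**4. Can a difference be hidden?** Assume 9% of women are abused (the protocol gives 8-10%), all of them score positive, and true disclosure rises from 20% to 35%. A further x% of all MOVE women score positive without disclosing.

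| x | MOVE restricted rate | Restricted difference |
|---|---|---|
| 0 | 3.15/9 = 35% | 15 points |
| 1 | 3.15/10 = 31.5% | 11.5 points |
| 3 | 3.15/12 = 26.25% | 6.25 points |
| 6 | 3.15/15 = 21% | 1 point |

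Among all respondents the rates are 0.20 × 9% = 1.80% and 0.35 × 9% = 3.15%, a difference of 1.35 points for every x.

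**5. Cost in power.** Document inputs are 5000 mailed per arm, 55-65% response, intra-cluster correlation (ICC) 0.02 and four teams per arm. Assumed inputs are two-sided alpha 0.05, 9% abused and the rates in step 4. The protocol's 5000 per arm cannot be reproduced, because alpha, power and baseline disclosure are not given; nothing here depends on it.

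Design effect = 1 + (m − 1) × ICC, with m respondents per team; power is by the normal approximation for two proportions. At 60% response:

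- All respondents: n = 3000, m = 750, design effect 15.98, effective n 188. Power for 1.80% v 3.15% is about 13%. It is about 21% at ICC 0.01 and 34% at ICC 0.005 (assumed lower values for a rare outcome).
- CAS-positive only: n = 270, m = 67.5, design effect 2.33, effective n 116. Power for 20% v 35% is about 73% (71-74% over the response range).

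Neither figure allows for having only eight clusters, so both are optimistic.

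**The case against.** Several points on the other side stand.

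- Disclosure and referral are most meaningful among abused women, and the sample size reasoning starts from the proportion abused. Replacing the restricted rate with the all-respondent rate as sole primary outcome would leave a comparison with about 13% power on the figures above.
- Comparison nurses must screen too. Where being asked or disclosing raises CAS reporting equally in both arms, the bias vanishes (third row of the first table).
- CAS prevalence by arm is already planned, so a large shift in the denominator would be seen. It would not be corrected, however, and equal prevalence does not rule out bias, because shifts in reporting and severity can offset each other.
- With four teams per arm, chance imbalance in abuse is a fair reason to want adjustment. A post-intervention CAS cannot separate such imbalance from an effect of MOVE.
- The contingency tables suggest that an unadjusted comparison of inquiry will appear anyway.

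A reader might infer more than the document supports. Conditioning on abuse status is not a literal breach of intention-to-treat, since women stay in the arm to which their team was allocated; it is a problem of estimand and bias. Nor is there evidence of a false gain of a particular size in favour of MOVE. The 2 to 4 points in the first two rows depend on reporting rising among MOVE disclosers alone, and the 5.6 points need MOVE non-disclosers to report less, against the recognition argument.

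**Conclusion.** The concern holds for the survey outcomes. Disclosure and offered referral are restricted to, and inquiry is stratified by and adjusted for, a variable measured after allocation in the same questionnaire, which MOVE could plausibly shift. The restricted comparison can then create or hide an arm difference. In the assumed examples, false differences run from −3.8 to +5.6 points, and a true 15-point rise shrinks to between 11.5 and 1 point, the last needing CAS prevalence to move from 9% to 15%. These are illustrations; the document fixes neither sign nor size.

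The point does not extend to the routine nurse data on inquiry, safety plans and referrals, which are not conditioned on the CAS. Nor does it show that the CAS-restricted results should be dropped.

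**What to change.** 1. Being asked: take survey abuse status out of the main model. Use all respondents and adjust only for factors the intervention cannot change. Give results by abuse status as secondary.
2. Disclosure and offered referral: report the all-respondent comparison, which for disclosure is the quantity the primary outcomes list defines, alongside the CAS ≥3 and ≥7 results. State that the latter condition on a post-allocation variable.
3. Interpret the CAS-restricted results next to the CAS prevalence by arm already planned, with a simple sensitivity analysis for differential CAS reporting, such as varying a and s by arm as above.

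The data are already to be collected, so the cost is analysis wording and a few extra tables, settled before unblinded analysis. The drawback is that all-respondent disclosure differences are small and imprecise; that limited power should be stated and the restricted rates kept.

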##### For MOVE primary outcomes

we will report:

• Any difference in proportions by trial arm (from survey and routine data) of screening for IPV (questions about fear of a partner; physical abuse and concern about the safety of their children) will be reported separately and as a screening inquiry composite variable

• Any difference in proportions by trial arm of women reporting IPV (Composite Abuse Scale ≥ 3 and ≥7) who have discussed IPV with their MCH nurse

• Any difference in proportions by trial arm of nurses who have reported that they have made safety plans with women clients

• Any difference in proportions by trial arm of women reporting IPV (Composite Abuse Scale ≥ 3 and ≥7) who have been offered a referral (if sufficient numbers) or nurses who report they have made referrals for IPV (routine data)

The following measures will be reported for the overall population and also by trial arm.

• Any difference in proportions by trial arm of abused and non-abused women reporting satisfaction with their MCH nursing care

• Intimate partner violence measured by the Composite Abuse Scale reported for women with scores ≥ 3 and those with scores ≥ 7

• Proportions ever having been afraid and currently afraid of their partner

• Proportions reporting partner abuse during pregnancy for the recent pregnancy and any in a past pregnancy.

• Proportions abused in pregnancy by family members and by other known persons (e.g. employer, housemate)

• Proportions physically, sexually, emotionally abused or neglected as children

• Proportions reporting harm from IPV screening or participating in an IPV screening study

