#### Blinding (outcome assessment)

All outcome and process evaluation data are self-completed by women and nurses and are anonymous:

(a) MCHN staff complete process and impact survey instruments on line using an anonymised format and data are stored in a secure database

(b) MCHN complete anonymised routine computerized screen data that are summarized annually and forwarded to the Department of Education and Early Childhood Development

(c) Names and addresses of women attending MCH clinics are not accessible to research staff because of privacy regulations. Surveys are sent to women in anonymised questionnaire booklets mailed to their home by a local government agency with an accompanying letter from their MCHN team leader. Outcomes were pre-specified at the time of our trial registration. Analyses are to be carried out by the study statistician blinded for trial arm following data entry of women’s survey responses by an independent data company.

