### Outcome measures

#### Routine data

Data reported routinely to the Victorian government is entered at the time of consultation by the MCH nurse. In relation to IPV screening, these data include:

• Whether the nurse reports asking about any of three family violence questions to which the answer is yes/no and at what time point: home visit; four weeks, eight weeks, four, eight, twelve or eighteen months.

• Whether the nurse reports making a safety plan

• Whether the nurse reports making a referral

We will compare rates of inquiry, safety plans and referrals between intervention and comparison arms at four weeks, four months and twelve months.

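### Safety plans, and the routine-data version of referral, are primary outcomes counted per nurse in one section and as rates at set visits in another; the per-nurse form varies with caseload

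*Protocol article*

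**What the plan says.** Three sections of the protocol article bear on the unit of analysis.

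- **For MOVE primary outcomes** (analysis section). Safety plans are reported as "Any difference in proportions by trial arm of nurses who have reported that they have made safety plans with women clients". Referral has two forms. The first is the proportion of women with abuse on the Composite Abuse Scale "who have been offered a referral (if sufficient numbers"). The second, joined by an or, is "nurses who report they have made referrals for IPV (routine data").
- **Routine data** (under Outcome measures). "Data reported routinely to the Victorian government is entered at the time of consultation by the MCH nurse". The items include whether a safety plan and whether a referral was made. The planned comparison is: "We will compare rates of inquiry, safety plans and referrals between intervention and comparison arms at four weeks, four months and twelve months".
- **Primary outcomes list.** Referral is a proportion of referrals, or of women offered one. The safety-plan part reads "nurses reporting discussing safety plans", which can be taken as a count of nurses or as a label for the data source.

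On the form of the data, Blinding (outcome assessment) says "MCHN complete anonymised routine computerized screen data that are summarized annually". The Outcome evaluation section says routine data will be retrieved for all nurses in both arms and mentions no nurse identifier.

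**The concern.** A proportion of nurses who have made a safety plan is not a rate of safety plans at four weeks, four months or twelve months. Both are planned for a primary outcome, and the same split affects the routine-data version of referral. Two analysts following different sections would report different primary results.

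The choice matters because a has-made-one measure has two properties that a rate lacks. It gives a nurse with one plan the same weight as a nurse with many. It also rises with the number of clients a nurse sees, so a difference in caseload or part-time working between teams could be read as an intervention effect, or could hide one. With eight teams, such differences need not balance between arms.

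**Working it through.** **1. The sections side by side**

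| Outcome | Primary outcomes list | Routine data section | For MOVE primary outcomes |
|---|---|---|---|
| Safety plans | nurses reporting (unit unclear) | rate at three visit ages | proportion of nurses |
| Referrals, nurse-reported | proportion of referrals | rate at three visit ages | proportion of nurses |
| Referrals, woman-reported | proportion of women | not applicable | proportion of women with abuse |

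For safety plans the conflict is between the second and third columns. For nurse-reported referral the third column differs from both others. The woman-reported referral outcome is consistent. The safety-plan bullet names no data source, but routine data are the only source for which the article lists safety plans.

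There is no figure in the plan to reproduce: it states no rate, effect size or power for safety plans or referrals. The 5000 questionnaires per arm are sized on disclosure in the women's survey.

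**2. Dependence on caseload**

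Inputs from the article: 10,000 births in 8 months (women's survey section); over 160 nurses (Design), taken as 160; 8–10% of women abused in the previous 12 months (sample size section), midpoint 9%.

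Assumptions: births scale to 12 months, caseloads are even apart from the contrast shown, events are independent, and a share p of abused women get a plan.

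- Mothers per nurse-year: 10,000 / 160 × 12/8 = 93.75.
- Abused clients per nurse-year: k = 93.75 × 0.09 = 8.44.
- Chance that a nurse has made at least one plan: 1 − (1 − p)^k.

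At p = 10%:

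- Full caseload: 1 − 0.9^8.44 = 58.9%.
- Half caseload (k = 4.22): 1 − 0.9^4.22 = 35.9%.
- Gap with identical practice: 23 points.

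The range over p at 9% prevalence:

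| p | Full caseload | Half caseload | Gap (points) |
|---|---|---|---|
| 5% | 35.1% | 19.5% | 15.7 |
| 10% | 58.9% | 35.9% | 23.0 |
| 20% | 84.8% | 61.0% | 23.8 |
| 40% | 98.7% | 88.4% | 10.2 |

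At p = 10%, prevalence of 8% or 10% gives gaps of 22.0 and 23.8 points. A rate per woman would be the same at either caseload.

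**3. Is the measure at a ceiling?**

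Let r be the plan rate per mother, abused or not. The share of nurses with at least one plan is 1 − (1 − r)^93.75:

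| r | Nurses with at least one | If r doubles |
|---|---|---|
| 0.25% | 21% | 37% |
| 0.5% | 37% | 61% |
| 1% | 61% | 85% |
| 2% | 85% | 98% |
| 3% | 94% | 99.7% |
| 5% | 99% | over 99.9% |

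The measure approaches its ceiling from about 2–3% per mother upward, and not at 1% or below. The documents do not give r.

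**The case against.** The strongest reply is that the wording about nurses reporting names the data source (nurse rather than woman), and that the analysis bullets use the same shorthand, with the Routine data section giving the operational comparison. The Routine data section itself states no denominator, so a rate per visit is an inference. An article may leave exact denominators to an analysis plan. That may explain how the wording arose, but it does not settle the unit: the analysis bullets name nurses as those whose proportion is compared, and that is a stated quantity rather than omitted detail.

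Teams were stratified by births and paired in size, which might be thought to deal with caseload. It does not, because pairing on births per area does not balance births per nurse. Equally, no section shows that caseloads differ between arms, so the 23-point gap is a property of the measure and not a predicted bias.

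A reader might go further in four ways that the documents do not support.

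- *That referral is analysed only per nurse.* A woman-level survey proportion is listed first.
- *That the nurse-level measure saturates.* This depends on a plan rate the article does not give.
- *That it shrinks the effect and gives a weaker result.* At 9% prevalence, a doubling of p from 5%, 10% or 20% gives nurse-level risk ratios of 1.7, 1.4 and 1.2. On other scales the picture changes. The odds ratios rise from 2.1, 2.25 and 2.7 per abused woman to about 2.6, 3.9 and 13 per nurse. The differences go from 5, 10 and 20 points to about 24, 26 and 14. The planned report is of differences in proportions, so shrinkage is not general.
- *That nurse counts cannot be obtained.* The annual anonymised summary goes to the Department, and the extract retrieved with local government permission may be different. The documents neither confirm nor exclude a nurse key.

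**Conclusion.** The point holds as an inconsistency of unit in primary outcomes. Safety plans, and the routine-data alternative for referral, are proportions of nurses in the analysis section and rates at three visit ages in the Routine data section. The primary outcomes list also words referral differently from the per-nurse bullet.

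Taken literally, the per-nurse form varies with caseload when practice does not: about 59% against 36% at an assumed 10% plan rate when caseload is halved, and gaps of about 10 to 24 points over assumed rates of 5% to 40%. These figures rest on the assumed plan rates, births scaled to a year, 160 nurses and independent events. They show how the measure behaves and do not estimate bias in this trial. Neither a ceiling, nor a general loss of effect, nor unobtainable data is established. The wording should be corrected because it decides what a primary result means.

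**What to change.** Reconcile the primary outcomes list, the Routine data section and the section For MOVE primary outcomes. Define the routine-data outcomes as the number of safety plans, and the number of referrals, per woman attending (or per consultation) at four weeks, four months and twelve months. Compare them by arm with allowance for clustering by team (local government area), as the article already plans for its models. Keep the proportion of nurses for the online nurse survey only. Leave the woman-level survey referral outcome as stated.

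Before adopting this, confirm that the extract supplies the number of women attending, or of consultations, at each of those visits, since no section says that it does. The cost is a change of outcome wording and a request for attendance counts with the routine data.
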